### Recruitment and consent

Children who eligible for the trial are clinically assessed when they attend their initial outpatient visit. Discuss about the management of IXT with the parents or guardians and provide the information about the SOMIX study. Parents or guardians who express an interest and possibility of taking part are then given written information of the SOMIX study. At the recruitment clinic, eligibility is confirmed by checking the results of the initial clinical assessment against the inclusion criteria. The informed consent for participation is obtained from those who decide to participate into the trial.

The following routine clinical assessments are undertaken in order to confirm the eligibility of the participants:BSV testingBCVAMeasurement of ocular alignment using PACT at near and distanceRoutine ocular examination of anterior segment, fundus, and ocular motility

**Fig. 2 Fig2:**
[figure not shown]
Standard protocol item. The follow-up visits schedule and corresponding clinical assessments. D, day; W, week; M, month; Y, year; BSV, binocular single vision; BCVA, best corrected visual acuity; PACT, prism and alternative cover test; NCS, Newcastle control score; IXTQ, intermittent exotropia questionnaire

Children in the observation group will be offered surgical treatment if a constant strabismus appears to be developing or parents request surgery and the responsible clinical team agrees that this is appropriate.

### Post-trial care

The study will provide post-trial care and insurance for those who suffer adverse events from trial participation.

### Allocation

#### Sequence generation

A blocked allocation (permuted random blocks of variable length) system is being used to randomly allocate patients to the two groups in a 1:1 ratio to intervention (group A) and control (group B) groups.

#### Concealment mechanism

Authorized ophthalmologists followed corresponding treatments for enrolling participants based on grouping information.

#### Implementation

Authorized ophthalmologists will enroll and assign participants. Participants are informed of their group allocation and given the appropriate group allocation information sheet.

### Proposed outcome measures

Primary outcome

For children with IXT, and their parents, the most relevant outcome from intervention is the restoration of normal ocular alignment, with associated cosmetic and functional benefits. The primary outcome of this RCT study will therefore be the difference in the cure rate of IXT between the surgical treatment and observation group.

Cure of IXT will be defined as:Realignment of ocular position at last follow-up, with deviation less than 8 PD both at near and distanceImprovement of near and distance stereoacuity ≥ 2 octaves (≥ 0.6 log arcsec)b)Secondary outcomeImprovement of NCSAge-specific evaluation of quality of life (IXTQ)Change of refraction

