**Methods/design:**

A total of 280 patients between 5 and 18 years of age with moderate IXT will be enrolled at Zhongshan Ophthalmic Center, Sun Yat-sen University, Guangzhou, China. After initial clinical assessment, all participants will be randomized to receive surgical treatment or observation, and then be followed up for 5 years. The primary objective is to compare the cure rate of IXT between the surgical treatment and observation group. The secondary objectives are to identify the predictive factors affecting long-term outcomes in each group and to observe the natural course of IXT.

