## Introduction

### Background

Strabismus is a common ophthalmic condition in children with prevalence of 1–5% [1–7], and intermittent exotropia (IXT) in which the eyes intermittently drift outward is one of the most common types of strabismus in childhood [8]. IXT left untreated can result in decreased stereopsis and amblyopia [9] and could eventually lead to intelligence and psychosocial problems [10, 11].

In clinical practice, the strabismus surgery can be performed in order to realign the eyes in severe IXT without binocular single vision (BSV). However, in children with mild IXT who have relatively normal BSV and good control of ocular alignment, the clinicians and parents prefer an observation rather than surgical or conservative treatments [12–14]. The best treatment and optimal timing of intervention for IXT remain unclear [15, 16], particularly for children with moderate IXT who manifest obvious exodeviation frequently but with only partial impairment of BSV. Previous retrospective study showed long-term surgical outcomes in small angle IXT did not appear to be more satisfying than observation [12]. The lack of randomized controlled trial (RCT) evidence means that the true effectiveness of the surgical treatment in curing moderate IXT is still unknown, or even when surgery is the preferred option, there is little agreement on the optimal timing for the surgery in this condition [15, 17, 18]. So, here, in the present study, we conducted a randomized trial of children 5 to 18 years of age with moderate IXT to assess the effectiveness of surgical treatment compared with observation for improving the ocular alignment and stereoacuity over long-term period of 5 years.

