### Objectives

The primary objective of the SOMIX trial (NCT 02,736,526) is to compare the long-term cure rate of IXT between the surgical treatment and observation group. The secondary objectives are to identify the predictive factors affecting long-term outcomes in each group and to observe the natural course of IXT.

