### Sample size

The sample size for this study was calculated based on a standard two-sided trial with a continuous outcome, and the calculations assume 5% type I error with 80% power. According to an average 30% dropout rate in long-term follow-up period, we anticipate that we will require 280 total participants.

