### Statistical methods

The participant will be included in the analysis, once be randomized, regardless of whether or not the assigned intervention is received, in order to follow the “intention-to-treat” design.

For primary outcome, a chi-squared test will be carried out to evaluate the difference in cure rate at the final assessment between groups. For secondary outcome, a chi-squared test will be used to compare rates of improved NCS outcome between groups; Student’s *t*-tests will be used to assess the validity by matching individual initial and final scores.

Statistical significance was set at *p* < 0.05. Data were analyzed with the SPSS statistical package [SPSS (Statistical Package for the Social Sciences) Inc., Chicago, IL, USA], version 19.

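### The primary endpoint has no fixed time: neither cure component nor the primary test is tied to the 5-year visit, so earlier results may enter the long-term cure rate

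*Protocol article*

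**What the plan says.** **Endpoint.** Under Proposed outcome measures, cure has two components. Alignment is read as "Realignment of ocular position at last follow-up". The stereoacuity gain (at least 2 octaves, near and distance) is given no visit.

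**Analysis.** Statistical methods plans a chi-squared test to "evaluate the difference in cure rate at the final assessment between groups". The final assessment is not defined. The same section sets the analysis population: "The participant will be included in the analysis, once be randomized, regardless of whether or not the assigned intervention is received".

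**Horizon.** The abstract says that participants will be randomised "and then be followed up for 5 years". Background describes effectiveness "over long-term period of 5 years". Objectives says the aim is to "compare the long-term cure rate of IXT between the surgical treatment and observation group".

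**Attrition.** Sample size allows for an "average 30% dropout rate in long-term follow-up period", with no timing and no split by arm. Dropout criteria lists different triggers by arm: adverse events after surgery in the surgical arm, and emerging constant strabismus or a parental wish for surgery in the observation arm.

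**The concern.** A cure rate needs a time. Here the question is set at 5 years, but the outcome that answers it is read at a visit the text does not pin down. With every randomised child in the analysis and almost a third expected to leave, the literal instruction is to score each child at whichever visit came last. A result from well before year 5 could then be counted alongside true 5-year results.

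The reasons for leaving are related to outcome and differ between arms, so early results need not enter both arms in the same number or with the same meaning. The stereoacuity component raises a second problem: with no visit named, the two halves of cure could be taken from different visits.

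At stake is the trial's only primary comparison. Two analysts following the article could reach different primary results from the same data.

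**Working it through.** **Inputs from the protocol article.** Total 280, allocation 1:1, two-sided 5% type I error, 80% power, 30% average dropout. No cure rates, effect size, standard deviation or dropout times are given.

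**The plan's own figure.** Without an effect size, 280 cannot be reproduced from stated inputs. Working backwards:

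- 280 × 0.70 = 196 children remaining, or 98 per arm.
- The implied standardised difference is (1.960 + 0.842) × √(2/98) = 0.40.
- Forwards, an assumed 0.40 gives 99 per arm, and 198 / 0.70 = 283, close to 280.

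So 280 is consistent with a target of about 98 per arm after losses.

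**Children affected.** 280 / 2 = 140 per arm, and 140 × 0.30 = 42 per arm (84 in all) would have no 5-year visit if dropout is equal in the arms.

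**Shift in one arm.** Suppose leavers are scored at their last visit and would have had the arm's 5-year rate had they stayed. Then

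rate at last visit available = 0.70 × (5-year rate) + 0.30 × (leavers' rate at last visit),

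shift = 0.30 × (leavers' rate at last visit − 5-year rate).

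| Assumed gap (points) | Shift (points) |
|---|---|
| −20 | −6 |
| −10 | −3 |
| 0 | 0 |
| +10 | +3 |
| +20 | +6 |
| +30 | +9 |
| +40 | +12 |

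A gradual version: if cure falls linearly from 60% to 35% and leavers go uniformly over 5 years, their mean last-visit rate is (60 + 35) / 2 = 47.5%. The arm then reads 0.70 × 35 + 0.30 × 47.5 = 38.75%, a shift of +3.75 points.

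**Shift in the between-arm difference.** This is 0.30 × (surgical gap − observation gap). Three illustrations, all with assumed rates:

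- Surgery 40% at year 5 and 70% at the leavers' last visit, observation 10% throughout: surgery reads 0.70 × 40 + 0.30 × 70 = 49%, so the difference is 39 points instead of 30.
- Surgery 40% at year 5 and 20% at the leavers' last visit (for example, leavers with complications not yet cured), observation 10% throughout: surgery reads 28 + 6 = 34%, so the difference is 24 points instead of 30.
- 20% in both arms at year 5, surgical leavers at 60%, observed leavers at 20%: rates read 14 + 18 = 32% and 20%. With 140 per arm the chi-squared test is significant about 63% of the time, although the 5-year rates are equal.

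The last case is deliberately unfavourable. It shows that the time anchor can change the conclusion, not that it will.

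**The case against.** The strongest reply is that the article means the scheduled 5-year visit. Follow-up is planned for 5 years for everyone, the final assessment is in the singular, and the visit schedule sits in a figure not available here. The sample-size section points the same way: if every leaver's last value counted as an observed outcome, there would be little reason to inflate for dropout. The intention-to-treat sentence concerns receipt of the assigned treatment and is not a rule for missing outcomes. All of this stands, and it leaves the question open: neither term is tied to year 5, and the stereoacuity component has no time at all.

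A reader might infer two stronger claims that the article does not support.

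- **That the plan carries the last observation forward.** No such rule is written. It is what the literal wording would produce, not what the article says will be done. Nor does it give dropout times, so it is not known that the results concerned would be early post-operative ones.
- **That the bias favours surgery.** The surgical dropout trigger is an adverse event, and such children may be uncured when last seen, which would count against surgery. Children leaving observation are deteriorating or seeking surgery, so they are not obviously forgoing spontaneous improvement. Cure also requires a stereoacuity gain, and the Discussion notes that good alignment does not ensure recovery of binocular vision, so a fall in composite cure over time cannot be assumed. Different triggers also do not show that follow-up length differs between arms.

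The particular missing-data method may sit in an analysis plan not shown, and its absence is not counted here.

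**Conclusion.** The point holds as an unfixed time anchor in a stated primary endpoint. The wording admits at least two analyses: all 140 per arm at their last available visit, or about 98 per arm at year 5 with 42 missing. These can give different cure rates.

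The size depends on quantities the article does not supply. At 30% dropout, the shift in an arm's rate is zero if cure is stable over time and about 3 to 6 points for assumed gaps of 10 to 20 points, in either direction. This assumes equal dropout in the arms and leavers who would have matched the arm's 5-year rate. The effect on the between-arm difference depends on both arms' gaps, and its sign is not established. The change is cheap and worth making because it settles what the primary result means.

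**What to change.** In Proposed outcome measures, define cure as both components met at the 5-year visit, with a stated window, in both arms. In Statistical methods, replace the undefined final assessment with that visit.

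State that the 5-year visit is still sought, where possible, for children who meet a dropout criterion, so that the intention-to-treat population has outcomes to analyse. Treat children without the visit as missing under a method stated in advance, with a sensitivity analysis such as counting them as not cured. Keep the last-available-visit analysis as a sensitivity analysis only.

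The cost is wording and some analysis work. No visits are added to the 5 years already planned, although tracing children who meet a dropout criterion may take effort. The confidence interval will be somewhat wider than if last-visit values were counted as observed. If leavers contributed nothing, the factor would be about √(140/98) = 1.20 at the same rates, and a method that uses their interim data may recover part of that. The plan's 280 already appears to allow for about 98 per arm.

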### Data management

#### Data collection

An electronic data capture (EDC) system will be used to collect study data, including baseline characteristics and follow-up clinical evaluations. Participants will be mandatorily followed up regularly in order to access the necessary information.

#### Confidentiality

All data collected in this study will be strictly protected. Participants in the EDC system will be allocated an individual trial identification number to protect confidentiality before, during, and after the trial.

#### Plans to promote participant retention and complete follow-up

Appropriate medical advices and “green channel” of follow-up visit will be provided to participants if they adhere to the protocol and complete follow-up. The trial steering committee will remind the participants the follow-up time in advance through message or phone call.

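### Two retention benefits depend on undefined adherence, which risks adherence-related missing outcomes in an intention-to-treat analysis

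*Protocol article*

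**What the plan says.** All references are to the protocol article.

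- **Plans to promote participant retention and complete follow-up.** Medical advice and a green-channel follow-up visit "will be provided to participants if they adhere to the protocol and complete follow-up". The next sentence has no such condition: "The trial steering committee will remind the participants the follow-up time in advance through message or phone call".
- **Data collection.** "Participants will be mandatorily followed up regularly in order to access the necessary information". This has no adherence condition either.
- **Statistical methods.** "The participant will be included in the analysis, once be randomized, regardless of whether or not the assigned intervention is received". The primary analysis is a chi-squared test of cure at the final assessment.
- **Interventions, text below Fig. 2.** "Children in the observation group will be offered surgical treatment if a constant strabismus appears to be developing or parents request surgery", provided the clinical team agrees.
- **Dropout criteria.** Observation children who appear to be developing constant strabismus, or whose parents ask for surgery, are listed as dropouts. So are surgical children with an adverse event or serious adverse event after the operation.
- **Sample size.** The total of 280 allows for an "average 30% dropout rate in long-term follow-up period".

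The article does not say what adhering to the protocol means.

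**The concern.** An intention-to-treat comparison is only as good as the outcomes collected from children who did not receive, or did not stay on, their assigned management. A retention benefit that depends on adherence gives those families less reason to return. It is also partly circular, since a measure meant to secure complete follow-up is promised on condition of completing it.

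Two groups could be affected. Surgical-arm children who never have the operation fit the ordinary sense of non-adherence. Observation children who go on to surgery are affected if they are counted as non-adherent, or if they are treated as dropouts under the Dropout criteria and so cannot complete follow-up.

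If surgery raises the chance of cure, selective loss of crossovers lowers the observed cure rate in the observation arm, and selective loss of unoperated children raises it in the surgical arm. Both make surgery look better than the intention-to-treat contrast would show. This is a matter of what the retention rule states, not of detail left to a fuller document.

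**Working it through.** **The plan's own figure.** The retention section contains no number. The only related figure is the 30% dropout allowance: 280 × (1 − 0.30) = 196 evaluable, or 98 per arm at 1:1. The allowance is a single average. It says nothing about whether loss differs by arm or by management received.

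**Inputs for an illustration of the observation arm.** Only the 70% is tied to the document (1 − 0.30). The rest are assumptions.

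- x, share crossing to surgery: 10% to 30%
- c_x, cure in crossovers: 30% to 50%
- c_n, cure in the others: 5%
- r_n, retention of the others: 70%
- r_x, retention of crossovers: 70%, 50% or 30%

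**Formulas.**

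- Intention-to-treat rate = x·c_x + (1 − x)·c_n
- Observed rate = [x·r_x·c_x + (1 − x)·r_n·c_n] / [x·r_x + (1 − x)·r_n]

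**Largest case (x = 30%, c_x = 50%).**

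- Intention-to-treat rate: 0.30 × 0.50 + 0.70 × 0.05 = 18.5%.
- r_x = 50%: (0.075 + 0.0245) / (0.15 + 0.49) = 0.0995 / 0.64 = 15.5%, a gap of about 3.0 points.
- r_x = 30%: (0.045 + 0.0245) / (0.09 + 0.49) = 0.0695 / 0.58 = 12.0%, a gap of 6.5 points.

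**Smallest case (x = 10%, c_x = 30%).**

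- Intention-to-treat rate: 0.03 + 0.045 = 7.5%.
- r_x = 50%: 0.0465 / 0.68 = 6.8%, a gap of 0.7 points.
- r_x = 30%: 0.0405 / 0.66 = 6.1%, a gap of 1.4 points.

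| x | c_x | ITT rate | Gap, r_x = 70% | Gap, r_x = 50% | Gap, r_x = 30% |
|---|---|---|---|---|---|
| 10% | 30% | 7.5% | 0 | 0.7 | 1.4 |
| 30% | 50% | 18.5% | 0 | 3.0 | 6.5 |

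When r_x = r_n the retention terms cancel and the gap is zero whatever x and c_x are. The bias comes entirely from unequal retention.

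**Sensitivity to how the 70% is read.** If 70% is instead the retention of the whole observation arm, retention of non-crossovers must rise as crossovers are lost. In the largest case with r_x = 30% it becomes (0.70 − 0.09) / 0.70 = 87%. The observed rate is then (0.045 + 0.61 × 0.05) / 0.70 = 10.8%, a gap of 7.7 points. With r_x = 50% it is (0.075 + 0.55 × 0.05) / 0.70 = 14.6%, a gap of 3.9 points. I prefer 70% for non-crossovers, because nothing suggests that they would be retained better than planned.

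The effect in the surgical arm is not sized here. Its direction is as described above.

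**The case against.** A reader might infer that retention support goes only to adherent families, so that loss will follow crossover. The documents do not support that, for four reasons.

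1. Reminders go to participants without condition, follow-up is described as mandatory, and the section on potential risks promises active monitoring of both groups throughout follow-up. Only medical advice and green-channel visits are conditional. This stands, and it limits the point to those two measures. It does not remove the point: a reminder is not the same as easier access to a visit, and the plan itself expects 30% loss despite the mandatory wording.
2. Surgery in the observation arm is a route that the protocol provides for, so a child who takes it may well be adhering. Under a heading about retention, adherence may simply mean keeping the visit schedule. This stands as a fair reading. The Dropout criteria point the other way, because a child classed as a dropout can hardly complete follow-up. The term needs defining or removing.
3. No crossover rate, no differential-loss rate and no evidence that lacking a green-channel visit causes loss is given. This stands. Risk is the most that can be claimed.
4. If every crossover were lost, the observed rate would fall to 5% and the gap would be x × (c_x − c_n): 0.10 × 0.25 = 2.5 points up to 0.30 × 0.45 = 13.5 points. That describes treating crossovers as dropouts, so it belongs to the Dropout criteria and should not be charged to the retention sentence.

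**Conclusion.** The point holds in a limited form. Making two retention benefits depend on undefined adherence works against an analysis of everyone randomised, and risks missing outcomes that depend on adherence. It clearly reaches surgical-arm children who never have surgery. It reaches observation children who cross over only if they count as non-adherent or as dropouts.

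The size is illustrative. Under the stated assumptions the observation-arm cure rate would be understated by about 0.7 to 3 points if crossovers are retained at 50%, by about 1.4 to 6.5 points at 30%, and not at all if they are retained as well as the others. The documents do not say which applies. The point is minor, and worth acting on because the remedy costs almost nothing.

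**What to change.** Replace the condition in the retention section with wording such as: *Medical advice and green-channel follow-up visits are offered to every randomised participant for the full 5 years, whether or not the assigned management was received or changed.* Reminders need no change.

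Report retention by arm and by management received, so that readers can see whether loss was differential.

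Reconcile the Dropout criteria with the surgery provision below Fig. 2 and with the intention-to-treat statement, so that outcomes are still collected after crossover or an adverse event. This concerns data collection only and leaves the treatment rules as they are.

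The cost is one sentence, a few more fast-track visits and a slightly weaker incentive to stay on the assigned management. The change can still help: the Trial status section extends recruitment to October 2022, and 5 years from then runs to October 2027.
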